**1. Introduction**

**1.1 Obesity and Diabetes: Magnitude of the problem**

The results of the last national survey, the Australian Diabetes, obesity and lifestyle study (AusDiab), highlighted the rapid and dramatic rise in the prevalence of diabetes and other categories of abnormal glucose tolerance in Australia [1]. Indeed, almost one in four adult Australians had abnormal glucose tolerance in 2000, one of the highest prevalences reported in a developed nation. This epidemic of diabetes is explained, for the most part, by the coincident doubling in the prevalence of obesity over the last 20 years [2].

Accumulating evidence also suggests that vitamin D and calcium play a physiological role in the modulation of systemic inflammation [3-5], renin-angiotensin system [6], pancreatic β-cell function [7-9] and insulin action [10-14]. It could then be expected that a deregulation of these systems leads to type 2 diabetes, hypertension, metabolic syndrome, and cardiovascular disease (CVD).

**1.2 Observational Studies that Support the link between Vitamin D and Calcium Deficiency and type 2 Diabetes, Metabolic Syndrome and CVD**

Seasonal variation in the incidence of type 2 diabetes [15] and deterioration of glycemic control reported at the end of the winter [16], when vitamin D stores reach their nadir, first pointed toward a possible link between vitamin D deficiency and impaired glucose metabolism. Studies reporting higher prevalence rates of vitamin D deficiency in type 2 diabetics compared to normal controls further supported this hypothesis [5, 17]. It is worth noting that this difference persisted even after adjustment for body-mass index (BMI), which had been shown to independently predict low serum levels of 25-hydroxyvitamin D (25OHD), a reliable marker of vitamin D status [18, 19].

Most experts now consider that the optimal cut-off for 25OHD should be 75 nmol/L [20, 21]. Two recent large cohort studies reinforced the choice of this cut-off for maintenance of normal glucose homeostasis [22, 23]. The first study showed a 60% relative risk reduction (RRR) between the highest and lowest quartiles of 25OHD, which had a mean 25OHD level of 70.9 and 22.4 nmol/L, respectively. The second study showed a 75% RRR between the highest and lowest quartiles of 25OHD (25OHD levels of >80 versus <44 nmol/L, respectively). Recently, an inverse nonlinear correlation, stronger with higher BMIs, was described between 25OHD and HbA_1_C, reaching a plateau at a level of 65 nmol/L [24]. In addition, high serum 25OHD levels have been associated with decreased CVD prevalence among type 2 diabetics, probably mediated by the anti-inflammatory properties of vitamin D [5]. Finally, vitamin D deficiency was the only predictive factor for metabolic syndrome in a population study of severely obese subjects (Odds ratio: 3.1, 95% CI 1.15-8.4, P=0.022) [25].

The protective effect of vitamin D and calcium supplementation on diabetes risk was suggested by the association of high dairy intake with decreased risk of insulin resistance syndrome, mainly in overweight or obese subjects [26]. In the Nurses’ Health Study, a combined daily intake of >1200 mg of calcium and >800 IU of vitamin D conferred the lowest risk of type 2 diabetes (RR: 0.67, 95% CI 0.49-0.9), and was more effective than either taken alone [27]. This effect remained when adjusting for co-variates such as age, BMI and family history.

**1.3 Physiological Roles of vitamin D and Calcium in the Regulation of Glucose homeostasis, Blood Pressure and Inflammation**

***Vitamin D, Calcium and Insulin Secretion***

The discovery of vitamin D receptor and calcium-binding protein expression in pancreatic β cells in the late 1970’s [28, 29], and also more recently, of 1α-25-hydroxylase activity, the enzyme that converts 25OHD into its active metabolite (calcitriol) [30], suggests a role of vitamin D in insulin secretion. Calcium has long been known to play a crucial role in hormone release [31]. Indeed, the first phase of insulin secretion is dependent mainly on β cell intracellular calcium stores whereas the second phase relies both on intra and extracellular calcium stores [32]. Earlier studies in rats showed that vitamin D deficiency impairs insulin secretion, which could be improved by calcitriol supplementation [33-35]. Of note, these studies were performed in vitamin D deficient and hypocalcemic rats. Well-known consequences of vitamin D deficiency are hypocalcemia and secondary hyperparathyroidism. Since these abnormalities could be reversed with adequate vitamin D supplementation, whether the benefits of vitamin D supplementation on insulin secretion could be attributed to vitamin D, independently of its role in calcium and parathormone (PTH) normalisation remains unclear. Indeed, calcium supplementation alone has been shown to increase insulin secretion in vitamin D deplete rats [36, 37]. However, it is reasonable to speculate that the effects of vitamin D and calcium on β cell are additive. Besides its role in maintaining adequate extracellular calcium concentrations, calcitriol has been shown to increase transcription of preproinsulin and calcium-binding proteins (which maintain optimal intracellular calcium reserves for first phase insulin secretion) [38].

***Vitamin D, Calcium and Insulin Sensitivity***

The precise mechanisms through which VD and calcium improve insulin sensitivity are unclear. Calcium has been shown to increase the binding affinity of insulin to its receptor [13] and to promote insulin-mediated glucose transport in adipocytes [14]. The role of VD on insulin sensitivity may rely, at least in part, on a direct stimulatory effect on insulin receptor expression [10] and on modulation of inflammation [3, 5]. Macrophages that reside in the adipose tissue of individuals with type 2 diabetes produce pro-inflammatory cytokines that have been incriminated in the pathophysiology of type 2 diabetes. The expression of VDR and 1α-25-hydroxylase in a wide range of inflammatory cells including monocytes and macrophages results in increased local production of calcitriol inside these cells which then regulates cytokine production by the activated lymphocytes [39]. An *in vitro* study evaluating the effect of VD on isolated monocytes from patients with type 2 diabetes demonstrated that these inflammatory cells decreased their production of pro-inflammatory cytokines such as IL-1, IL-6, IL-8 and TNF-α when exposed to calcitriol [3]. These findings suggest that VD may directly improve insulin sensitivity through modulation of inflammation.

***Osteocalcin and adiponectin as possible novel indirect mediators of effects of vitamin D on insulin sensitivity***

Type 2 diabetes is characterised by the combination of impaired pancreatic β-cell secretion of insulin, and resistance to insulin action in the body. Circulating adiponectin secreted by adipocytes correlates strongly with insulin sensitivity, and negatively with visceral obesity. Furthermore, circulating adiponectin is reduced in patients with type 2 diabetes [40]. Osteocalcin is a novel regulatory mechanism linking bone formation with glucose metabolism via regulation of both β-cell insulin secretion and adiponectin [41]. Mice lacking an osteoblast-expressed receptor-like protein tyrosine phosphatase (*Esp* -/-) displayed increased β-cell proliferation and insulin secretion, and were protected from diabetes. This phenotype was corrected by deletion of a single allele of osteocalcin. In accordance with these findings, osteocalcin knockout mice (*Ocn* -/-) were glucose intolerant and overweight, implicating this osteoblast-secreted circulating molecule as a novel regulator of glucose homeostasis. *Ocn* -/- mice exhibited reduced β-cell mass and pancreatic insulin content, and reduced adiponectin expression and low serum adiponectin levels, similar to humans with type 2 diabetes mellitus. These findings were reversed by treatment with recombinant osteocalcin or co-culture with osteocalcin-expressing fibroblasts. Finally, *Esp* -/- mice had comparable serum osteocalcin as wild-type controls [41], but a lower proportion of gamma-carboxylated osteocalcin, as reflected by reduced binding of serum osteocalcin *in vitro* to hydroxyapatite. Osteocalcin lacking gamma-carboxylation was the metabolically active form, which induced expression of adiponectin in adipocytes. These findings represent a new paradigm of regulation of energy metabolism by the skeleton, with non-gamma-carboxylated osteocalcin acting as a new hormone and systemic stimulator of insulin and adiponectin secretion [42]. VD may also have a role in gamma-carboxylation of osteocalcin [43].

***Vitamin D and Regulation of the Renin-Angiotensin System***

Finally, calcitriol appears to be a strong down-regulator of the renin-angiotensin system through direct suppression of the renin gene promoter activity [6]. Indeed, renin expression and angiotensin II concentration are increased in VDR-null mice, leading to hypertension.

**1.4 Effects of vitamin D and Calcium Supplementation in Humans**

Inconsistent results have been reported from the few studies that evaluated the effect of vitamin D supplementation on glucose homeostasis [44-50]. In summary, no clear effect of vitamin D supplementation on insulin secretion or insulin sensitivity was found in lean, normal glucose tolerant and vitamin D replete subjects [46]. Most studies of glucose intolerant and vitamin D sufficient individuals have not shown a benefit from treatment with vitamin D [48, 49]. However, one study showed that vitamin D supplementation in severely vitamin D deficient Asians at high risk for type 2 diabetes (95% of the population had 25OHD levels < 24 nmol/L) increased insulin and C-peptide levels post glucose load compared to vitamin D deficient individuals at low risk for the disease [47]. A significant increase in first phase insulin secretion and non significant increase in second phase insulin secretion and insulin resistance was also noted after vitamin D supplementation in a small sample of vitamin D deficient type 2 diabetic females [50]. Only one study in humans evaluated the combined effect of vitamin D and calcium supplementation on glucose homeostasis [45]. Of note, this study was designed for primary skeletal outcomes. However, treatment with 700 IU of vitamin D_3_ and 500 mg of elemental calcium for 3 years in overweight and vitamin D sufficient people with impaired fasting glucose prevented the increase in fasting plasma glucose and insulin resistance observed in the placebo group.

**2. Rationale of Project**

Taken together, evidences from *in vitro*, animal and observational human studies suggest that vitamin D and calcium supplementation improve the metabolic profile of vitamin D deficient individuals. It is also reasonable to expect from the physiological roles calcium and vitamin D seem to play on insulin secretion and sensitivity that their effects are additive. However, calcium and vitamin D supplementation trials have yielded contradicting results. Many factors could explain this discrepancy. First, the baseline vitamin D and glucose tolerance status of the selected populations is very heterogeneous between studies. In addition, the main shortcoming of these papers is the lack of ascertainment of adequate vitamin D supplementation. Targeting optimal 25OHD levels is particularly important, since based on observational studies, an improvement in glucose homeostasis is expected at 25OHD levels over 65-80 nmol/L [22-24]. To conclude from these studies, we expect that the group to benefit most from the intervention would be those with vitamin D deficiency at high risk for type 2 diabetes. Those in the early stages of the disease, when irreversible β cell failure has not yet occurred, would seem appropriate to target due to the beneficial effects seen on insulin secretion.

To our knowledge, the study we propose is the first specifically designed to assess the combined effect of adequate calcium and vitamin D supplementation on glucose homeostasis and metabolic profile on vitamin D deficient subjects at high risk of developing type 2 diabetes. If a beneficial effect of treatment is demonstrated, it could have major implications on the prevention and treatment of this escalating disease.

**3. Aims/Hypothesis**

**3.1 Primary Aim**

The primary aim of this study is to determine if adequate vitamin D supplementation (2000-4000 IU of vitamin D_3_ daily, assessed by a serum 25OHD level of ≥75 nmol/L) and calcium supplementation (1200 mg daily) in vitamin D deficient individuals at high risk of type 2 diabetes improve:

- Insulin sensitivity (homeostasis model assessment of insulin resistance – HOMA-IR);
- Glucose-stimulated insulin secretion (insulinogenic index and deconvolution analysis of C-peptide levels after a glucose load);
- Beta-cell function (disposition index).

**Primary Hypothesis:** Combined treatment with VD and calcium will significantly improve the insulin sensitivity, glucose-stimulated insulin secretion and β-cell function of VD deficient men and women at high risk of type 2 diabetes compared with placebo.

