**5.5 Procedures**

Pre-randomisation measurements

To ensure the inclusion and exclusion criteria are met, a 24h urine collection for calcium and blood tests for 25OHD, calcium, albumin and renal function must have been done in the last month. A 75g 2h OGTT result no more than 3 months old must also be available.

Measurements at baseline and at the end of the study

*Anthropometrical and blood pressure assessments**

- Height (to the nearest 0.5 cm), using a wall-mounted stadiometer;
- Body weight (to the nearest 0.1 kg), measured without shoes and in light clothing, using an electronic calibrated scale;
- Waist circumference (to the nearest 0.5 cm), using a tape placed at the midpoint between the lower rib and the upper iliac crest;
- Blood pressure, taken 3 times in the sitting position with an adequate pressure cuff, after a 5-minute rest. The mean of the 3 results will be used for statistical purposes.

*These parameters will also be measured at 2 months

*Body composition*

Fat mass will be measured using dual-energy X-ray absorptiometry (Hologic, Discovery W, Bedford, MA, USA) only at the beginning of the study to correlate fat mass with the dose of vitamin D_3_ needed to reach optimal 25OHD levels.

*Biochemical assessments*

- Fasting blood will be drawn for 25OHD, total calcium, albumin, phosphate, PTH, alkaline phosphatase, osteocalcin, complete lipid profile, HbA_1_C, FFAs, adiponectin, high-sensitive C-reactive protein (hs-CRP) and fibrinogen;
- 2h OGTT after 75g of glucose: glucose, insulin and C-peptide levels will be measured at times -30, -20, -10, 0, 10, 20, 30, 60, 90 and 120 minutes;
- 24h urinary calcium and creatinine;
- Extra aliquot for storage for measurement of other bone markers and markers of inflammation (IL-6 and TNF-alpha) and diabetes when the funds will be available.

*Questionnaires*

- Medical history;
- Food questionnaire to estimate vitamin D and calcium intake [56];
- Physical activity questionnaire [57];
- Questionnaire to estimate sunlight exposure.

*Assessment of β-cell insulin secretion, insulin resistance and beta-cell function*

- **Insulin secretion rate** will be estimated by two methods:
  - The insulinogenic index ([Ins_t30_ – Ins_t0_] ÷ [Glucose_t30_ – Glucose_t0_]), which mainly reflects the first phase of insulin secretion;

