  - The deconvolution analysis of C-peptide levels after a glucose load. C-peptide is probably a better indicator of insulin secretion than insulin itself since the latter is subject to hepatic clearance. Pre-hepatic ISR will be calculated from deconvolution of peripheral plasma C-peptide levels using a two compartment mathematical model with standard parameters for C-peptide distribution and metabolism, as previously described using the Chronobiological Series Analyses software (iBridge Network, [www.iBridgeNetwork.org](http://www.iBridgeNetwork.org), University of Chicago) [58]. Use of standard parameters for C-peptide clearance and distribution has been shown to result in insulin secretion rates that differ in each subject by only 10-12% from those obtained with individual parameters and there is no systematic over- or underestimation of insulin secretion. Incremental ISR from baseline during the first 30 minutes divided by incremental glucose and absolute total area under the curve of C-peptide by deconvolution analysis will be compared between baseline and 6 months of treatment.
- **Insulin resistance** will also be assessed by two methods:
  - The homeostasis model assessment for insulin resistance (HOMA-IR) is particularly suitable for obese and/or glucose intolerant subjects and has been shown to highly correlate with measures of insulin sensitivity obtained from the gold-standard procedure (euglycemic clamp technique) [59-61]. It is calculated from fasting insulin and glucose levels as follows: [Fasting insulin (mU/L) X fasting glucose (mmol/L)] ÷ 22.5.
  - Insulin resistance will also be estimated with the revised Quicki index: 1/[log (fasting glucose in mg/dl) + log (fasting insulin in μunits/ml) + log (fasting FFA). This index was shown to better correlate with euglycemic clamp than HOMA-IR in impaired glucose tolerant individuals (r=0,802) [62].
- **Beta-cell function** will be estimated by calculating the disposition index (DI): DI = insulin sensitivity (HOMA-IR) X ISR (deconvolution analysis of C-peptides).

*Evaluation of compliance*

Pill count will be performed after two months and at the end of the study to verify compliance to medication. Participants will be asked to report any change in their medication since the last visit.

*Monitoring of side effects and Safety Issues*

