**5.6 Statistical analyses**

Analyses will be performed using SPSS version 15.0. Skewed data will be log-transformed or examined using non-parametric tests. Differences in delta HOMA-IR between the treatment and the placebo group will be compared by two-sample unpaired *t* test. The change in DI and in ISR (assessed by deconvolution analysis of C-peptide levels and the insulinogenic index) and also the total area under the curve of C-peptide by deconvolution analysis will be compared between groups with unpaired *t* test. Analyses will be performed to assess changes in inflammatory markers, intact osteocalcin, adiponectin, blood pressure, lipid profile, FFA and weight with a two-sample unpaired *t* test. A *P*-value of ≤0.05 will be considered statistically significant. The endpoints will be adjusted for risk factors of type 2 diabetes: age, sex, BMI, family history of type 2 diabetes and physical activity. The following covariates will also be adjusted for: sunlight exposure and VD and calcium intake. Finally, the variables that predict response to treatment will be identified with multiple linear regression analyses. We will perform data analysis on an intention-to-treat principle. We will also perform analysis on patients who achieved >75% compliance with study medication as well as those on active treatment who achieved target 25OHD levels ≥75 nmol/L.

*Sample size calculation*

Sample size calculation is based on the difference in delta HOMA-IR [0.15 ± 0.18 (SD)] observed in a similar population of overweight subjects with pre-diabetes before and after a mean weight loss of 9.8 kg [64]. This change in HOMA-IR resulted in improved beta-cell function and reduction in the area under glucose curve during OGTT. This change in HOMA-IR was therefore considered clinically significant and was chosen for sample size calculation. A sample of 32 participants in each group will have 90% power to detect a difference in delta HOMA-IR of 0.15 with a standard deviation of 0.18 and 2-sided alpha of 0.05. Assuming a drop out rate of 20%, we will study a total of 80 participants.

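### The primary hypothesis covers five separately tested outcomes with no success rule, so the 5% error rate (per test) and the 90% power (change in HOMA-IR only) cannot both carry over to the primary conclusion

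*Protocol*

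**What the plan says.** Section 3.1 of the protocol sets one primary aim and one primary hypothesis over three domains: "Combined treatment with VD and calcium will significantly improve the insulin sensitivity, glucose-stimulated insulin secretion and β-cell function". The measures attached to them are:

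- "Insulin sensitivity (homeostasis model assessment of insulin resistance – HOMA-IR";
- "Glucose-stimulated insulin secretion (insulinogenic index and deconvolution analysis of C-peptide levels after a glucose load";
- the disposition index (DI), for beta-cell function.

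That is four named measures. Section 5.5 repeats that insulin secretion "will be estimated by two methods", then takes two quantities from the deconvolution: "Incremental ISR from baseline during the first 30 minutes divided by incremental glucose and absolute total area under the curve of C-peptide". The total is then five: HOMA-IR, insulinogenic index, incremental ISR over incremental glucose, total C-peptide AUC, and DI.

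Section 5.6 compares the change in HOMA-IR between groups by unpaired t test, and does the same for DI, both ISR measures and the total AUC. A single threshold covers every test: a P-value "of ≤0.05 will be considered statistically significant".

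The sample size, also in 5.6, concerns one outcome: "A sample of 32 participants in each group will have 90% power to detect a difference in delta HOMA-IR of 0.15", with SD 0.18 and two-sided alpha 0.05. It is raised to 80 in total for 20% dropout. No effect size, SD or power is given for the other four outcomes.

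**The concern.** With one primary outcome, the significance level and the power describe the trial's main conclusion directly. With five outcomes under one hypothesis they do so only once the plan says which combination of results supports that hypothesis, and this protocol does not. If HOMA-IR were null and the insulinogenic index gave P = 0.03, the protocol would not settle whether the primary hypothesis had been supported.

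The choice would then fall to whoever reads the results. A lenient reading raises the chance of a false claim; a strict one leaves the trial with less power than the sample size section suggests. Either way, a figure the reader relies on describes something other than the primary conclusion.

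**Working it through.** **Inputs from the documents.** Difference 0.15, SD 0.18, two-sided alpha 0.05, 32 per arm, 20% dropout (5.6); 1:1 allocation (5.2); three domains (3.1); five outcomes (3.1, 5.5, 5.6).

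**Assumptions, not in the documents.** A common correlation ρ between the test statistics, varied from 0 to 0.9; and 90% power for every outcome, because only HOMA-IR has an effect size and SD.

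**Step 1. Reproduce the plan's figure.**
- Normal approximation: n = 2(1.96 + 1.2816)² × (0.18/0.15)² = 30.3, so 31 per arm.
- Noncentral t: 32 per arm. The noncentrality is (0.15/0.18) × √(32/2) = 3.33 on 62 degrees of freedom, giving 90.7% power.
- Dropout: 64/0.80 = 80.

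The stated figures are right, for change in HOMA-IR alone.

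**Step 2. Any one significant result suffices.** Under independence the chance of at least one false positive is 1 − 0.95^k: 14.3% for k = 3 (one outcome per domain) and 22.6% for k = 5.

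**Step 3. All results must be significant.** Under independence, power is 0.90^k: 0.729 for k = 3 and 0.590 for k = 5.

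Correlated cases were simulated with equicorrelated normal statistics (400,000 draws):

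| ρ | Any of 3: error | Any of 5: error | All 3: power | All 5: power |
|---|---|---|---|---|
| 0 | 14.3% | 22.6% | 73% | 59% |
| 0.3 | 13.7% | 20.9% | 76% | 66% |
| 0.5 | 12.6% | 18.4% | 78% | 71% |
| 0.7 | 10.9% | 14.9% | 81% | 76% |
| 0.9 | 8.3% | 10.2% | 85% | 83% |

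**Step 4. What survives under each rule.**
- *Any one suffices:* the error rate exceeds 5%. Power for at least one success is no lower than the HOMA-IR power, so about 90% remains a floor.
- *All required:* this is an intersection-union test, so type I error stays at or below 5%. Power cannot exceed the HOMA-IR power, because HOMA-IR is one of the required results.
- *Mixed rule, for example all three domains with any one of the three secretion measures enough:* if only secretion is null, the error can reach 1 − 0.95³ = 14.3%. With 90.7% power per measure and independence, power is 0.907² × (1 − 0.093³) = 82%. Here both figures fail.

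**The case against.** **A statistical analysis plan may settle this.** A multiplicity procedure or testing order is commonly left to that document, which is not at hand, so its absence from the protocol is not a fault by itself. That stands. But the joint primary hypothesis, the common threshold and the single-outcome power basis are fixed in the protocol. Section 3.2 lists secondary aims separately, so all three domains were ranked as primary. A later plan could not demote four outcomes without departing from 3.1.

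**A reader might infer that neither 5% nor 90% applies.** The documents do not support this as a general statement. The two figures fail under opposite rules, and both fail together only under a mixed rule that the protocol does not state.

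**A reader might infer that the trial may be declared positive on any one of five tests.** Section 5.6 gives only a per-test threshold. The word *and* in the hypothesis, read literally, points to requiring all.

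**A reader might infer from 5.8 that a fall in secretion could count as benefit, leaving the direction of success open.** That sentence concerns physical activity and weight change as sources of bias. It says nothing about which direction of secretion is favourable.

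**The magnitudes depend on assumptions.** This stands too. The documents give no correlations, and a common value is only a simplification: "DI = insulin sensitivity (HOMA-IR) X ISR (deconvolution analysis of C-peptides" ties DI by construction to two other measures. The 22.6% also counts differences in either direction. For false claims of benefit alone it is 1 − 0.975⁵ = 11.9% under independence, against 2.5% for one test. The loss of power under an all-required rule could be small if the other outcomes were very well powered: at 99% each, 0.90 × 0.99⁴ = 86%.

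**Conclusion.** The point holds in conditional form. The protocol puts five tests under one primary hypothesis and fixes neither a lead outcome nor a success rule. The 5% is a per-test rate and the 90% is the power for change in HOMA-IR. At least one of them fails to describe the primary conclusion under any reading that uses more than one outcome, and the protocol does not show which.

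For five outcomes, an any-one rule gives a two-sided error rate from about 10% (assumed correlation 0.9) to 22.6% (independence). An all-required rule keeps the error at or below 5% and caps power at the HOMA-IR value. How far below that cap it falls depends on assumed power and correlations; the 59–76% for five outcomes and 73–81% for three are illustrations at 90% each and correlations of 0 to 0.7. The sample size arithmetic itself is correct.

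**What to change.** In 3.1 and 5.6, name change in HOMA-IR, the only outcome on which the trial is sized, as the single primary outcome at two-sided 0.05. Make DI, insulinogenic index, incremental ISR and total C-peptide AUC key secondary outcomes, either tested in a pre-stated order or reported with confidence intervals, and reword the primary hypothesis to match. This is a change of wording only; 32 per arm and 80 in total stand. The cost is that secretion and beta-cell function lose a stand-alone primary claim, a real loss because section 2 uses the expected effect on secretion to justify the population.

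If the sponsor prefers to keep all three domains primary, the protocol should state the success rule and the power that goes with it. An all-required rule needs an effect size and SD for each outcome. A Bonferroni split on the HOMA-IR inputs shows the price of the alternative:
- three tests: power at 32 per arm falls to 80.6%; 90% needs 41 per arm, or 82/0.80 = 102.5, so 103 in total;
- five tests: power at 32 per arm falls to 74.8%; 90% needs 45 per arm, or 90/0.80 = 112.5, so 113 in total.
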